## Materials and methods

Study design and population

It is a parallel-arm, diagnostic study design. The study population will include individuals between 18 and 50 years of age, consulting for mandibular third molar removal, that have an intimate relationship with inferior dental nerve.

Clinical and radiographic inclusion criteria

Healthy patients or those with controlled co-morbid conditions who are willing to undergo surgery for removal of impacted mandibular wisdom teeth in the age group of 18 to 50 years will be included in the study. Radiographic inclusion criteria include a close approximation of the inferior dental canal to roots of mandibular wisdom teeth, as evidenced by the observance of one or more of the following signs, visible on OPG, namely darkening of the root, narrowing of the canal, dark and bifid root, diversion of the mandibular canal, deflection of the roots, interruption of the white line of the mandibular canal wall, and narrowing of the roots [11].

Clinical and radiographic exclusion criteria

Patients with uncontrolled co-morbidities (American Society of Anesthesiologists (ASA) 3 or higher), a history of nerve disorders or diseases affecting nerves (such as neuralgia or stroke), any existing pathology (like cyst or tumor), previous CBCT scan, or those not willing to undergo surgery for removing impacted lower wisdom teeth will be excluded from the study. Pregnant patients will also be excluded. Patients with impacted lower wisdom teeth that are not closely associated with the inferior alveolar neurovascular bundle will comprise radiographic exclusion criteria.

Participant recruitment

Adults (between 18 and 50 years) with one or two lower wisdom teeth in close approximation to the inferior dental canal (as observed on OPG) following the above stated clinical and radiographic inclusion/exclusion criteria shall be incorporated into the study. The patients will be intimated about the course of the study, the possible consequences, the further line of management, and their informed consent will be taken. The patients will be recruited and randomly assigned to either of the two groups (OPG group and CBCT group) using a random computer generation sequence. The allocation concealment will be ascertained by contacting the principal investigator for group allocation.

In the OPG group, the patients will be subjected to digital OPG alone (Planmeca Promax-Planmeca, Helsinki, Finland). In the CBCT group, a high-resolution CBCT scan will be done for the mandible preoperatively in addition to baseline OPG (Planmeca Promax 3D - Planmeca, Helsinki, Finland). CBCT/OPG images will be assessed by experienced surgeons. They will decide their surgical steps based on information from the OPG/CBCT images. All lower wisdom teeth will be removed using local anesthesia by standard surgical protocol with odontectomy. Variables, including the operating surgeon’s experience, will be noted down along with the outcome variables of subjective and objective nerve injury from day one till six months after surgery. The CONSORT flow diagram showing the progress of the study is outlined in Figure 1.

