The investigator assessing the primary and secondary outcomes will be blinded to the groups. The number of patients reporting subjective symptoms of inferior alveolar nerve injury after surgery will be considered as the primary outcome. The secondary outcome will include the number of patients experiencing signs and symptoms of nerve injury that are confirmed by an abnormal clinical neurosensory test. It will also include those patients having symptoms of injury lasting more than six months post-surgery. First, the patients will be enquired about abnormal sensations in the ipsilateral lip and chin and compared to the contralateral side. This will be confirmed by standard clinical quantitative nerve testing procedures such as static light touch, two-point discrimination, brush-directional discrimination, and pin pressure nociception [21]. Patients with altered sensation will be examined at day one, day seven, day 30, day 60, day 90, and then day 180 postoperatively to assess their recovery pattern. If needed, further consultations will be taken for persistent paresthesia/anesthesia.

Training and calibration of personnel

Trained oral and maxillofacial surgeons will carry out the assessment independently. They will be experienced in the identification and diagnosis of maxillofacial structures utilizing both OPG and CBCT. They will be blinded by the clinical outcome. All three planes will be assessed through the implant planning screen and multiplanar reconstruction screen.

Mitigation of confounders

There can be various confounders in this study. First of all, the patients will be randomized to the two groups based on a random computer generator sequence to avoid selection bias. Group allocation will be done by contacting the principal investigator for randomization. Experienced surgeons will be carrying out the procedure, and their experience will be noted down. Besides, it will be performed by different surgeons for external validation. The type of impaction will be noted to assess difficulty. The technique of surgical removal will be standard, involving odontectomy. The evaluator of the outcome will be blinded to the group of study participants.

Sample size calculation

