## Results

The results will be described based on Standards for Reporting of Diagnostic Accuracy (STARD) guidelines. The statistical analyses will be done with the ‘intention to treat’ principle. The complete dataset analysis will encompass all study participants, based on the mentioned inclusion/exclusion criteria, who have no missing data for any of the parameters in the dataset. The primary outcome will include the number of patients experiencing inferior dental nerve injury as evidenced by the subjective presence of paresthesia, anesthesia, or dysesthesia after mandibular third molar surgery. Secondary outcomes will include the number of patients with nerve injury confirmed by abnormal clinical neurosensory testing and nerve injury lasting for more than six months.

Baseline characteristics will be used to describe data. Mean and standard deviation will be used to describe continuous variables. Frequencies and percentages will be used to describe categorical data. The outcome variables for continuous data, if normally distributed, will be summarized by using the mean, range, standard error, standard deviation, and confidence interval at 95%. The outcome variables for continuous data will be analyzed using an independent sample t test at the 5% level of significance (P<=0.05) assuming a normal distribution.

Data not following normal distribution will be described by nonparametric tests using mean, median, lower, and upper quartiles. A Mann-Whitney test will be used for testing such significance. Chi square analysis will be utilized to analyze efficacy for the categorical variables. Fisher exact or chi-square test will be used to analyze nominal and dichotomous data. Analysis for logistic regression will be done to recognize possible risk factors for impairment of the inferior alveolar nerve. Comparative groups will be analyzed by a t test at the 5% level of significance (P<=0.05). Sensitivity and specificity of CBCT and OPG in prediction of nerve injury will be confirmed on the basis of results obtained on subjective/objective nerve testing after surgical removal of a tooth (Table 1).

**Table 1 TAB1:** Master chart format for recording various study variables

	Demographic variables									Pathological variables			OPG findings							Cone beam computed tomography					Surgical variables							outcome variables													

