Patient	Age	Sex	ASA class	Medical co-morbidity	Smoking (frequency)	Alcohol (frequency)	Oral contraceptive use (Y/N)	Oral hygiene (good, moderate. Poor)	Side (38/48)	Pericoronitis (Y/N)	Pocket >4mm(Y/N)	Caries(Y/)	Angulation	Depth of impaction (A, B,C)	Ramus overlap (I, II,III)	Difficulty index	Length of red line (in mm)	Rood Shehab criteria (name/s)	Vertical over projection of root with inf alv canal Class 1,2,3,>3	Inf alv canal position in relation to root (inf, ling, buccal, inter-radicular)	Distance between root and IA canal vertically and buccolingually	Root in contact with IA canal (Y/N)	Cortical layer of canal (present/absent)	Shape of canal (round/oval/narrowing)	Experience of surgeon (<100 M3 removed, 101-500 M3 removed, 501-1000 M3 removed, 1001-3000 M3 removed, >3000 M3 removed)	Incision/flap (envelope/triangular/quadrilateral)	Bone removal (Y/N)	Odontectomy (Y/N)	No.of roots (1,2,>2)	Inf alv nerve visible (Y/N)	Intra-operative hemorrhage from IA canal	Subjective inf alv nerve injury (Y/N)						objective inf alv nerve injury (Y/N)						infection	any other complication
																																Day 1	Day 7	1 month	2 months	3 months	6 months	Day 1	Day 7	1 month	2 months	3 months	6 months		
1																																													
2																																													
3																																													
4																																													
5																																													
6																																													
7																																													
8																																													
9																																													
10																																													

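### Patients with two eligible teeth are admitted, but the master chart holds one side and one unsided injury entry per patient, so tooth-level findings can be linked to the wrong nerve

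*Protocol article*

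**What the plan says.** Under Participant recruitment, the protocol article accepts adults "with one or two lower wisdom teeth in close approximation to the inferior dental canal" and randomises by patient. No index tooth is named. The following paragraph says "All lower wisdom teeth will be removed using local anesthesia by standard surgical protocol with odontectomy", without stating whether two teeth in one patient come out together, at separate visits, or both within the study.

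The outcome text under Patient screening process counts patients: "The number of patients reporting subjective symptoms of inferior alveolar nerve injury after surgery will be considered as the primary outcome". For the assessment, "the patients will be enquired about abnormal sensations in the ipsilateral lip and chin and compared to the contralateral side", after which quantitative sensory tests confirm the finding.

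Table 1 has one numbered row per patient. Each row has a single side field (38 or 48), one set of OPG, CBCT and surgical fields, and one outcome entry per visit headed "Subjective inf alv nerve injury (Y/N"), with a matching objective entry. Neither outcome entry is split by side.

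The Results section plans two analyses that use tooth-level findings. Sensitivity and specificity are to be judged "on the basis of results obtained on subjective/objective nerve testing after surgical removal of a tooth". For risk factors, "Analysis for logistic regression will be done to recognize possible risk factors for impairment of the inferior alveolar nerve".

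**The concern.** Each of these rules works when a patient contributes one tooth. The eligibility text allows two, and for those patients the rules do not fit together.

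- **Linkage.** Angulation, depth, length of the red line, root contact, cortical layer and nerve visibility describe one tooth. The outcome entry describes the patient. If the injury is on the side not entered in the row, the imaging of one tooth is credited with the outcome of the other. This bears on the first two stated objectives: correlating imaging with nerve injury, and delineating risk factors.
- **Comparator.** If the other side has also been operated on, it is no longer an untouched reference.
- **Independence.** If site staff add a second row for the second tooth, the listed chi-square, Fisher and logistic methods make no allowance for two teeth in one mouth.

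A later analysis plan could add clustering. It could not recover a side that was never recorded.

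**Working it through.** **1. The plan's own sample size, and its unit.** Inputs from Sample size calculation: p1 = 0.25, p2 = 0.58, r = 1, 5% significance, 80% power.

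- Pooled p = (0.25 + 0.58)/2 = 0.415.
- First term: 1.96 × √(2 × 0.415 × 0.585) = 1.96 × 0.697 = 1.366.
- Second term: 0.842 × √(0.25 × 0.75 + 0.58 × 0.42) = 0.842 × 0.657 = 0.553.
- n = (1.366 + 0.553)² / 0.33² = 3.68 / 0.1089 = 33.8, so 34 per group and 68 in total.

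This reproduces the stated size with the printed Z(1-α/2) term. (The text calls the test one-tailed; that mismatch is a separate matter.) The calculation treats each patient as one observation, as do randomisation and the primary outcome. Bilateral patients therefore do not upset it.

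**2. What the chart does to a bilateral patient.** A hypothetical CBCT-group patient has both teeth removed. Tooth 38 has root contact with the canal and tooth 48 does not. The nerve on side 48 is injured. For illustration, take root contact as the positive imaging sign.

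| Recording | Resulting data |
|---|---|
| One row, side 38 entered | contact yes, injury yes: a true positive |
| One row, side 48 entered | contact no, injury yes: a false negative; tooth 38 disappears |
| Side-specific entries | tooth 38: contact yes, injury no (false positive); tooth 48: contact no, injury yes (false negative) |

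The result depends on which side was entered, and the first version turns two prediction errors into one success. The same row then enters the logistic regression.

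**3. If each tooth is given its own row.** With a share f of bilateral patients and within-patient correlation ρ, the mean cluster size weighted by teeth is m* = [(1 − f) + 4f]/(1 + f), and the design effect is 1 + (m* − 1)ρ. The documents give neither f nor ρ, so both are assumptions.

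- f = 10%, ρ = 0.3: m* = 1.3/1.1 = 1.182; design effect 1 + 0.182 × 0.3 = 1.05. A nominal two-sided 5% test has true error of about 5.6%.
- f = 30%, ρ = 0.3: m* = 1.9/1.3 = 1.462; design effect 1 + 0.462 × 0.3 = 1.14. True error is about 6.6%.
- f = 30%, ρ = 0.5: design effect 1 + 0.462 × 0.5 = 1.23. True error is about 7.7%.

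These figures apply most directly to factors that are the same for both teeth of a patient, such as study group or smoking.

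**4. The comparator.** The primary outcome in the Results section is the subjective presence of altered sensation, which a patient can report on both sides without any left-right difference. The contralateral comparison therefore matters less for the primary outcome than for the confirmatory testing behind the objective secondary outcome. It fails only when both sides have been operated on by the assessment date, and the timing is not stated.

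**The case against.** The strongest reply is that the randomised comparison is sound. Patients are randomised, patients are counted, and the sample size is based on patient-reported symptoms. Any injury per patient is a valid endpoint, and randomisation spreads bilateral patients over both groups in expectation. This stands in full.

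A reader might infer that symmetric injury would be scored as no injury and so bias the primary outcome. The documents do not support that: the definition asks for presence of symptoms, and the comparison with the other side accompanies the interview without being made a condition.

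A reader might also take 25% and 58% as per-nerve risks. With independent sides, that gives any-injury risks of 1 − 0.75² = 44% and 1 − 0.42² = 82%, with both nerves injured in 0.25² = 6% and 0.58² = 34%. The protocol ties those rates to patient-reported incidence and never calls them per-nerve. The figures would also hold only among patients operated on both sides; at an assumed 30% share, the double-injury figures fall to about 2% and 10% of a group. Likewise, a variance factor of 1.3 at correlation 0.3 requires every patient to be bilateral.

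It can also be said that the single side field, and the reference to removal of one tooth, suggest one study tooth per patient, and that row handling belongs in a case report form or analysis plan not shown. This stands in part. Nothing says that teeth will be analysed as independent, and clustering can be specified later. But the article prints both the two-tooth eligibility and the chart, and following that chart loses the side of injury for good.

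**Conclusion.** The point holds for the tooth-level analyses and for recording. In patients operated on both sides, the chart as printed cannot tie an injury to the tooth whose imaging and surgical findings are in the row. The sensitivity/specificity and risk-factor results can be mislinked as a consequence. Where both sides have been operated on before an assessment, the contralateral comparison is unreliable as well, chiefly for the objective secondary outcome.

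The per-patient primary comparison and the total of 68 stand. The amount of mislinking cannot be stated, because neither the bilateral share nor the timing of the two extractions is given. The standard-error problem arises only if teeth become independent rows. It is then modest: a variance factor of about 1.05 to 1.14 under the assumed 10-30% bilateral share and correlation of 0.3. This is an inexpensive improvement to make before data collection, not a flaw in the trial's main test.

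**What to change.** 1. Keep the primary outcome as any injury per patient. Restricting it to an index side would drop true injuries and change the endpoint.
2. In Table 1, record the imaging, surgical, and subjective and objective outcome entries separately for side 38 and side 48, with the date of each extraction.
3. Run the accuracy and risk-factor analyses per tooth, linking each tooth to its own side's outcome and using patient-clustered standard errors. Alternatively, use one tooth per patient in these analyses, picked at random before randomisation.
4. Flag every assessment made after both sides were operated on. Record each side's symptoms and test result on its own, not as a left-right difference, and add a sensitivity analysis that excludes these assessments.

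The cost is a few extra chart columns, some analysis work, and slightly wider intervals in the tooth-level analyses. The sample size does not change.

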**Figure 1 FIG1:**
[figure not shown]
CONSORT flow diagram [19]

Reference standard and its rationale

Orthopantomogram (OPG) is established diagnostic equipment that is used to assess the lower wisdom teeth and their relationship with the inferior dental nerve canal before surgery [10]. Due to challenges associated with the placement of the intraoral receptor during periapical radiography, for evaluating mandibular third molars, it is recommended to employ OPG as a primary imaging modality prior to surgical extraction. OPG is advantageous, as it can be conducted with minimal patient discomfort compared to intraoral techniques. Additionally, it is a low-radiation method that captures all wisdom teeth in a single film, equivalent to approximately two to 16 intraoral film exposures.

Patient screening process

In the assessment of OPG, the initial step involves determining if there is observance of one or more of Rood and Shehab’s criteria indicating close approximation between the root of the third molar and inferior alveolar canal. This will be the eligibility criteria for patient recruitment. All these patients will be assigned to either the OPG group or the CBCT group by random computer-generated sequence. Group allocation will be done by contacting the principal investigator for randomization. In the OPG group, patients will not be subjected to any other radiographs, whereas in the CBCT group, a CBCT will be done for the mandible in addition to the digital OPG used for screening. This is done to more accurately understand the spatial association between lower wisdom tooth roots and inferior dental canal. The OPG will be assessed for variables such as angulation, depth, difficulty index, length of red line, Rood Shehab’s criteria, as well as type of vertical overlap of third molar root with inferior alveolar canal [11,20].

CBCT images will be evaluated in all three planes. The images will be evaluated to find out the distance from the lower wisdom tooth root to the inferior dental canal and the continuity of the cortical layer between the neurovascular bundle and root. The spatial orientation of the inferior dental canal with regard to the wisdom tooth root will be noted down as either buccal, lingual, inferior, or interradicular. The shape of the IAC at the exact place of contact with the wisdom tooth root will be noted down as oval, round, or narrowed.

The investigator assessing the primary and secondary outcomes will be blinded to the groups. The number of patients reporting subjective symptoms of inferior alveolar nerve injury after surgery will be considered as the primary outcome. The secondary outcome will include the number of patients experiencing signs and symptoms of nerve injury that are confirmed by an abnormal clinical neurosensory test. It will also include those patients having symptoms of injury lasting more than six months post-surgery. First, the patients will be enquired about abnormal sensations in the ipsilateral lip and chin and compared to the contralateral side. This will be confirmed by standard clinical quantitative nerve testing procedures such as static light touch, two-point discrimination, brush-directional discrimination, and pin pressure nociception [21]. Patients with altered sensation will be examined at day one, day seven, day 30, day 60, day 90, and then day 180 postoperatively to assess their recovery pattern. If needed, further consultations will be taken for persistent paresthesia/anesthesia.

Training and calibration of personnel

Trained oral and maxillofacial surgeons will carry out the assessment independently. They will be experienced in the identification and diagnosis of maxillofacial structures utilizing both OPG and CBCT. They will be blinded by the clinical outcome. All three planes will be assessed through the implant planning screen and multiplanar reconstruction screen.

Mitigation of confounders

There can be various confounders in this study. First of all, the patients will be randomized to the two groups based on a random computer generator sequence to avoid selection bias. Group allocation will be done by contacting the principal investigator for randomization. Experienced surgeons will be carrying out the procedure, and their experience will be noted down. Besides, it will be performed by different surgeons for external validation. The type of impaction will be noted to assess difficulty. The technique of surgical removal will be standard, involving odontectomy. The evaluator of the outcome will be blinded to the group of study participants.

Sample size calculation

Hypotheses will be tested using the one-tailed superiority analysis method, with 80% power and a 5% level of significance, based on the incidence of patient-reported abnormal sensations after surgery. Considering a superiority margin of 33% as per reference values between the incidence of temporary inferior dental nerve paresthesia of 25% in the OPG group and 58% in the CBCT group, the total sample size will be 68 (34 in each group) using the following formula [18].

 \begin{document}p=(p_1+rp_2)/(1+r )\end{document}

\begin{document}n ≥ [Z_(1-α/2) √((r+1)p(1-p) )+Z_(1-β) √(rp_1 (1-p_1 )+p_2 (1-p_2 ) )]^2/(r (p_2-p_1 )^2 )\end{document}

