If a statistically significant result is obtained, then we can deliberately reduce CBCT referrals and reserve them only for high-risk cases, wherein the risk of IAN injury cannot be predicted by OPG alone. If the experience of the surgeon proves to be an important risk factor, then it can also help refer high-risk patients to surgeons with more experience.

Conclusion

If CBCT proves to be statistically superior to OPG in the prediction of nerve injury, then we will be able to avoid significant morbidity and improve the quality of life of such patients by either modifying the surgical steps or by choosing other conservative treatment modalities. Further, this may reduce unnecessary CBCT referrals, thus reducing radiation exposure, the cost to patients, and, in turn, national healthcare expenditure. Besides, CBCT is not available at all centers, so a lot of low-risk patients can be managed safely at primary health centers, thus reducing the urban patient load.

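### The sample size assumes more nerve injury with CBCT (58%) than with OPG (25%), against the benefit the article describes, and the one-tailed test has no stated direction

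*Protocol article*

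**What the plan says.** All of this is in the protocol article.

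- **Test (Materials and methods, Sample size calculation).** "Hypotheses will be tested using the one-tailed superiority analysis method, with 80% power and a 5% level of significance". No null or alternative hypothesis is written out, and the direction of the single tail is not given.
- **Endpoint.** The calculation is "based on the incidence of patient-reported abnormal sensations after surgery". The primary outcome is defined elsewhere in Materials and methods, and again under Results, as the number of patients with subjective nerve injury. A lower number is better.
- **Assumed rates.** "incidence of temporary inferior dental nerve paresthesia of 25% in the OPG group and 58% in the CBCT group", credited to reference 18. The 33% that the text calls a superiority margin is the difference between these two rates.
- **Size.** 34 per group, 68 in total, from a printed two-proportion formula that contains Z at 1 − α/2 and divides by the square of p2 − p1.
- **Hoped-for result (Abstract, Conclusion).** "If CBCT proves to be statistically superior to OPG in the prediction of nerve injury, then we will be able to avoid significant morbidity", either by changing the surgical steps or by choosing a more conservative treatment. Participant recruitment supplies the mechanism: surgeons plan their steps from the images they have.

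**The concern.** The assumed CBCT rate is 58/25 = 2.32 times the OPG rate, on an outcome where more is worse. Nothing in the article predicts that CBCT increases nerve injury, and nothing explains why its rate is the higher one. The only stated power is therefore, as printed, the power to find harm from CBCT, while the described benefit runs the other way.

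The calculation cannot expose this by itself, because squaring p2 − p1 gives the same N for either labelling. The unstated tail adds to the problem: a one-tailed test needs its direction fixed in advance, and here the assumed rates point one way and the described benefit the other.

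What is at stake is the reading of the result. If the trial is in fact poorly powered for a CBCT benefit, a non-significant result could be taken as evidence that CBCT adds nothing. The Abstract and Conclusions already look ahead to a policy of fewer CBCT referrals.

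**Working it through.** **Inputs** (Sample size calculation): p1 = 0.25 (OPG), p2 = 0.58 (CBCT), allocation ratio r = 1, α = 0.05, power 80%, critical value Z at 1 − α/2 = 1.960, Z at 1 − β = 0.8416.

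**1. Reproduce the plan's figure.**
- Average rate: p = (0.25 + 0.58)/2 = 0.415.
- First term: 1.960 × √(2 × 0.415 × 0.585) = 1.960 × 0.6968 = 1.3657.
- Second term: 0.8416 × √(0.25 × 0.75 + 0.58 × 0.42) = 0.8416 × 0.6566 = 0.5526.
- n = (1.3657 + 0.5526)² / 0.33² = 3.680 / 0.1089 = 33.79, so 34 per arm and 68 in total.

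The arithmetic is correct for the printed inputs.

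**2. One-tailed or two-sided?** With the one-sided value 1.645, the first term is 1.1462 and n = (1.1462 + 0.5526)² / 0.1089 = 26.5, so 27 per arm. The stated 34 therefore comes from the two-sided value, although the text says one-tailed.

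**3. Which direction does the power belong to?** Exact binomial enumeration, 34 per arm, OPG 25%, CBCT 58%, uncorrected chi-square (z) test, one-sided 5%:
- Probability of concluding CBCT higher: 0.891.
- Probability of concluding CBCT lower: 3.9 × 10⁻⁶, about 0.0004%.

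**4. If the labels are swapped** (OPG 58%, CBCT 25%). The formula is symmetric, so n stays at 34 per arm. Power for CBCT lower is 80.3% two-sided by normal approximation (80.9% exact), or 89.1% exact one-sided.

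**5. If 25% is the true OPG rate and CBCT is expected to be lower.** The highest CBCT rate for which the printed formula gives 34 per arm or fewer is:
- two-sided 5%: 0.021, about 2%;
- one-sided 5%: about 0.04, or 4%.

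For illustrative CBCT rates, which are assumptions and not taken from the article:

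| CBCT rate | n per arm, two-sided | n per arm, one-sided | Exact two-sided power at 34 per arm |
|---|---|---|---|
| 15% | 250 | 197 | 18% |
| 10% | 100 | 79 | 38% |
| 5% | 49 | 39 | 69% |

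The normal approximation gives 17%, 37% and 64% for the last column. Exact power is thus slightly higher at low rates, and the 2% and 4% limits should be read as results of the printed formula.

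**The case against.** The strongest reply is that the two labels were simply transposed. Step 4 shows that N and the 80% then stand in the benefit direction and only the sentence is wrong. This is a real possibility, and the article alone cannot exclude it. For that reason a reader should not infer that the 80% fails for the trial's question in every case, or that the corrected power must be worse. Both depend on what reference 18 reports. The Introduction says that the groups in that multicentre trial did not differ statistically and goes on to mention a reduced incidence of nerve injury. That sits oddly with reference rates 33 points apart and is a further reason to check, but it does not settle which figure is wrong.

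Second, no alternative hypothesis is printed, so the expected direction is inferred. Some text points elsewhere: the aim and the sensitivity and specificity analyses concern prediction, and the Abstract and Conclusions say that a significant result would allow fewer CBCT referrals. This stands as a caution. Still, for the primary outcome, a lower rate with CBCT is the natural reading of the morbidity statement and of surgeons acting on the images, and no text predicts the reverse.

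Third, a reader might infer that the trial could never declare a CBCT benefit. That would need a one-tailed analysis in the direction of the printed rates. The formula uses the two-sided value, and the Results section names a chi-square or Fisher test at 5% with no direction. If the analysis is two-sided, a benefit can be declared. What remains is the contradiction between the one-tailed wording and the two-sided formula.

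**Conclusion.** The point holds in conditional form. As printed, 68 patients and 80% power rest on rates that contradict the benefit the article describes, and the one-tailed test has no stated direction and does not match the two-sided formula. At the printed rates, one-sided power is 89% for CBCT higher and essentially zero for CBCT lower.

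The size of the consequence cannot be fixed from the article. Under a label swap, nothing changes but the text. If the OPG rate really is 25%, power in the benefit direction is well below 80% unless CBCT almost abolishes the injury; it is about 38% at an assumed CBCT rate of 10%. These figures assume 34 evaluable patients per arm and an uncorrected two-proportion test. The inconsistency itself is certain; which of the two cases applies is not.

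**What to change.** 1. Check both rates and their arm labels against reference 18, and correct them.
2. Write out the null and alternative hypotheses for the primary outcome, with the expected direction (CBCT lower than OPG).
3. Replace the one-tailed wording with a two-sided 5% test, so that the text matches the printed formula and the undirected tests in the Results section.
4. Restate the power for the benefit direction at 68 patients, using the corrected rates.

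The cost is a few sentences in the protocol, the same wording in any SAP, and one recomputed figure. The corrections themselves require no extra patients. The restated power may be less favourable; if 25% for OPG is confirmed, the sponsor will have to report the lower power openly or decide separately whether to enlarge the trial.
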